#### Blindness

Considerable efforts are made in this design to maintain the blindness of raters for the yearly face-to-face assessments including: written and verbal reminders to participants; a five-minute videotaped explanation of blindness by the principal investigator (GM) shown immediately prior to the 12-month assessment; and a reminder sign placed prominently in front of the participant during the course of the interview. Raters are asked to classify participants into a treatment condition together with any specific reasons for their guess and an estimate of their level of certainty. Breaches in rater blindness are addressed by changing the rater where possible.

### Statistical analysis

#### Primary outcomes

Intention-to-treat (ITT) analysis will be the primary analytic framework. Groups will be compared using chi-square or Fisher's exact test for proportions and *t*-test or Mann-Whitney-test for continuous variables. Time to relapse/recurrence of depression will be examined using the Kaplan-Meier survival analysis. The Cox proportional hazards regression analysis will be used to examine the effect of covariates such as treatment expectations on time to relapse/recurrence. Per protocol (PP) analyses will also be undertaken. As in previous trials, at least four sessions will be considered as the minimal treatment dose. However, as the MBCT program is sequential and participants are strongly encouraged to attend all sessions, or at least miss no more than one [63], we will also examine outcomes for people who attended the recommended dose of therapy, being 7-8 sessions.

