### Power analysis

A power analysis was conducted using estimates of annual relapse rates obtained from the literature. Systematic reviews and meta analyses were mainly utilised including: no treatment (or placebo) only [35-38]; psychological treatment alone; effect in recurrent depression of medication alone [35,37,38]; and combined psychological and pharmacotherapy [39,40]. From these sources, anticipated relapse rates over a 2-year period were: no treatment, 56%; MBCT alone, 31%; medication alone, 31%; and MBCT and medication together, 15%. Based on findings from recruitment in our pilot study, we assumed that 70% of the sample would be taking at least some reasonably effective dose of medication, and 30% would not. Applying the subgroup specific odds ratios suggested the following relapse rates as likely over a 26-month period: MBCT group 21.5%; and DRAM group 41.7%. A power analysis showed that to detect this difference using an uncorrected chi-squared statistic at 80% power and α = 0.05 would require a sample size of 82 participants to complete the full 26 months in each of the MBCT and DRAM groups [41]. Further, assuming a dropout rate of 20% led to a recruitment target of 102 participants for each group.

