#### Randomisation

Assignment of individual participants to MBCT + DRAM or DRAM alone is undertaken by the study statistician using a minimization routine balancing numbers in groups as randomisation proceeds [42]. The statistician works independently of staff involved in the recruitment, assessment and management of participants in the study. To guard against confounding by major differences in other treatment exposures, randomisation is stratified by: medication (currently taking antidepressants and/or mood stabilisers: yes/no); site of referral (primary care, secondary care, specialist clinic): diagnosis (bipolar disorder: yes/no); and gender.

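### The stated test of relapse ignores the four minimisation factors, and no single primary analysis is named; the cost is small and nearly free to remove

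*Protocol article*

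**What the plan says.** The Randomisation section describes a minimisation routine and states that "randomisation is stratified by: medication (currently taking antidepressants and/or mood stabilisers: yes/no"), followed by site of referral (three levels), bipolar diagnosis and gender. The reason given is protection against confounding by other treatment exposures.

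Statistical analysis, Primary outcomes, states "Intention-to-treat (ITT) analysis will be the primary analytic framework" and then "Groups will be compared using chi-square or Fisher's exact test for proportions". It adds Kaplan-Meier for time to relapse or recurrence, and a Cox model for covariates, with treatment expectations as its one example. According to the Procedure section, the expectancy questionnaire is given at weeks 4 and 8 of the program and 12 and 24 months after it, so it is not listed as a baseline measure. No analysis names the four allocation factors, and the proportion and time-to-event analyses are not ranked.

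The Power analysis section sizes the trial "using an uncorrected chi-squared statistic at 80% power and α = 0.05" on rates of "MBCT group 21.5%; and DRAM group 41.7" per cent over 26 months, which "would require a sample size of 82 participants to complete the full 26 months in each of the MBCT and DRAM groups". It then says that "assuming a dropout rate of 20% led to a recruitment target of 102 participants for each group". The Economic evaluation section ends with imputation sensitivity analyses for missing data across the analyses, and multilevel modelling where appropriate.

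**The concern.** Minimising on a prognostic factor makes the arms more alike on that factor than simple randomisation would. A test that leaves the factor out still counts its variation as noise, so its standard error is too large, its true level falls below the nominal 5%, and it gives up some power. The article supplies the evidence that medication is such a factor.

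The second issue is which analysis decides the trial. A yes/no chi-square needs a final status for everyone. The sizing counts the 82 per arm who complete, while the declared framework is ITT on all 102. Kaplan-Meier can use incomplete follow-up, but the article does not say whether it or the comparison of proportions carries the conclusion. If the two disagreed, the choice could be made after seeing the results.

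**Working it through.** **Inputs** (Power analysis section): 2-year relapse of 56% (no treatment), 31% (MBCT alone), 31% (medication alone) and 15% (both); 70% medicated; 26-month rates of 41.7% and 21.5%; 82 completers and 102 recruited per arm.

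**1. Reproducing the plan's figures.**
- Control: 0.7 × 31% + 0.3 × 56% = 38.5%; × 26/24 = 41.7%.
- MBCT: 0.7 × 15% + 0.3 × 31% = 19.8%; × 26/24 = 21.5%.
- n per arm = [1.96 √(2 p̄ q̄) + 0.842 √(p₁q₁ + p₂q₂)]² / (p₁ − p₂)², with p̄ = 0.316. This is (1.289 + 0.540)² / 0.202² ≈ 82, as stated (two-sided, no continuity correction).
- Dropout: 82 / 0.8 = 102.5, against 102 stated. Power is 80.0% at 82 per arm and 79.8% at 0.8 × 102 = 81.6. The sizing is sound for its own test.

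**2. Omitting medication.** Scaled by 26/24, control relapse is 33.6% in medicated and 60.7% in unmedicated participants.
- Variance between medication groups: 0.7 × 0.3 × (0.607 − 0.336)² = 0.0154.
- Total variance used by the chi-square: 0.417 × 0.583 = 0.2431.
- Share removed by balancing: 0.0154 / 0.2431 = 6.3%. The true standard error is √0.937 = 0.968 of the one used, the effective critical value is 1.96 / 0.968 = 2.025, and the large-sample level is about 4.3%.

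Simulation with both arms balanced on medication (200,000 trials per setting; CMH is the Cochran-Mantel-Haenszel test stratified on medication):

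| Per arm | Chi-square level | CMH level | Chi-square power | CMH power |
|---|---|---|---|---|
| 82 | 4.1% | 5.0% | 81.3% | 82.6% |
| 102 | 4.7% | 4.9% | 88.9% | 89.9% |

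The chi-square level differs between the two sizes because counts are discrete. The power gain is about 1 point at both.

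**3. The other three factors.** The article gives no effect for them. As an assumption only, let all factors together have a log-odds SD of 0.5, 1.0 or 1.5 (eight strata, 80 per arm, overall rates held at 41.7% and 21.5%). Chi-square power is then 80.1, 81.4 and 83.3%; CMH power is 80.8, 85.0 and 89.6%; the chi-square level is 4.1, 2.9 and 1.9%. The gain runs from under 1 to about 6 points.

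**4. Dropouts in a chi-square on all 102 per arm.** Coding the 20% as not relapsed gives rates of 0.8 × 41.7% = 33.4% and 0.8 × 21.5% = 17.2%, and power of 76.0%. Coding them as relapsed gives 53.4% and 37.2%, and power of 64.2%. The completer analysis has 80.0%.

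**5. Time to event.** Under exponential hazards, HR = ln(0.785) / ln(0.583) = 0.449, and power = Φ(√(D/4) × |ln HR| − 1.96) for D events.
- Completers only: D = 82 × (0.417 + 0.215) = 51.8; power 82%.
- Adding dropouts: 102 − 82 = 20 per arm. Assume uniform dropout over 26 months and CIDI interviews at months 14 and 26 (12 and 24 months after an 8-week program). Then 20 × 12/26 = 9.2 per arm leave after the first interview. Relapse by month 14 is 25.2% and 12.2%, so they add 9.2 × 0.374 = 3.5 events. D = 55.3; power 85%.

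**The case against.** The strongest reply is that this is a condensed article: adjustment covariates, dropout coding and the order of analyses are normally settled in an analysis plan, the Cox covariate list is open, and the trial was sized for this very chi-square. Much of that stands. The missing dropout rule alone would not be a finding. What remains is that the article does specify its test of proportions, and that test does not match the allocation it describes.

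Three stronger readings are tempting, and the documents do not support them.
- A reader might infer that the analysis is not ITT because the sizing counts completers. ITT is declared as the primary framework, an unadjusted test is compatible with it, and inflating 82 to 102 is an ordinary attrition allowance that does not define the analysis set.
- A reader might infer that dropouts have no valid place. Kaplan-Meier can censor them, a relapse recorded at the 12-month CIDI is known whatever happens later, and imputation is planned, though only as sensitivity analysis.
- A reader might infer a serious loss of power. The chi-square keeps its stated 80%; the loss is only relative to a better analysis, and a large one requires strong effects of site, bipolar diagnosis or gender that the article does not give.

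It is also fair to object that the time-to-event gain is limited by measurement: the CIDI is retrospective and yearly, so early leavers contribute nothing.

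**Conclusion.** The point holds as a modest inefficiency and an unfixed choice, not as an invalid analysis. On the article's own rates, omitting medication costs about 1 point of power and lowers the true level to about 4.1% at 82 per arm, assuming the arms are well balanced on medication and the rates scale by 26/24. Anything beyond that rests on assumed effects of the other three factors.

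The unranked analyses matter more for interpretation: power ranges from 64% to 85% across the ways shown of handling dropouts. That the chi-square is the primary comparison is only an inference from the sizing. The time-to-event advantage of about 3 points depends on exponential hazards, uniform non-informative dropout and the interview timing.

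**What to change.** Name one primary analysis in all randomised participants, stratified by or adjusted for medication, site of referral, bipolar diagnosis and gender. A stratified log-rank test or a Cox model on time to first CIDI-defined relapse is preferable, using the month of onset already collected, with dropouts censored at the end of the period covered by their last CIDI. Keep the unadjusted chi-square as supportive, and keep treatment expectations out of the primary model.

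This changes wording only, since the factors are known before allocation and onset month is already recorded. It has downsides that should be stated with it:
- Onset is dated only to the month.
- Participants who leave before the first follow-up CIDI contribute no CIDI time.
- The 12-month recall, taken 12 months after the program ends, may not cover the program weeks, so the time origin needs thought.
- The model assumes proportional hazards and non-informative censoring.
- With under 60 events expected it must stay small, so stratifying on all four factors at once would be too fine. Stratify on one or two and adjust for the rest.

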##### Patient Health Questionnaire

In the study the Patient Health Questionnaire-2 [PHQ-2 - [45]] and the PHQ-9 [46] are used to monitor for the presence and severity of depressive symptoms each month. The PHQ-2 is a screening tool for depression that comprises two questions addressing anhedonia and depressed mood with frequency ratings 0 (not at all) to 3 (nearly every day). The PHQ-9 comprises the nine criteria upon which the diagnosis of DSM-IV depressive disorders is based. Both instruments have been found to be reliable and valid [45,46]. As part of DRAM, participants are trained on how to complete the PHQ-2 and PHQ-9 then prompted monthly to self-monitor via their preferred medium of SMS, telephone or internet. To facilitate monitoring, the PHQ-2 is provided on a wallet card which also has their project ID and password for online completion. Participants reporting scores ≥3 are directed to complete the PHQ-9 and encouraged to seek appropriate assistance using automated feedback. The full PHQ-9 is administered every 3 months regardless of PHQ-2 score.

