### Procedure

#### Assessments

Experience from pilot work [62] indicated that the primary reason for exclusion from that study was failure to meet the selection criteria related to MDD. Referrals to the project are therefore screened over the phone using a brief questionnaire based on key questions from the Depression module of the Lifetime version of the CIDI 2.1. Potentially eligible candidates then are invited to complete an intake assessment to assess eligibility and collect baseline data. Following the intake assessment, eligible participants are randomised in cohorts to treatment condition. For participants in both treatment conditions, PHQ assessments are completed at intake and then at monthly intervals from the fourth week of the MBCT program conducted for their cohort. The CIDI 2.1 12 month version, Service Utilization, Hill-Bone Medication Taking Scale, IPPI, CEQ and Beliefs about Relapse are completed at 12 months and 24 months following the conclusion of the MBCT program. The CEQ is also administered at the fourth and eighth week of the MBCT program and Beliefs about Relapse at 8 weeks. The remaining self-report assessments are administered 3 monthly.

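### For PHQ severity, which the article places under the primary outcome without naming an analysis, the only tests on offer ignore the intake score; adjusting for it would be a free gain in precision

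*Protocol article*

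**What the plan says.** All references are to the Protocol article.

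- **Tests named.** Statistical analysis – Primary outcomes gives chi-square or Fisher's exact test for proportions, and the t-test or "Mann-Whitney-test for continuous variables". It adds Kaplan-Meier for time to relapse, and a Cox model whose covariates are illustrated by treatment expectations. It does not mention the PHQ.
- **Where the PHQ sits.** Patient Health Questionnaire is a subsection of Primary outcome: relapse/recurrence of MDD. There the PHQ-2 and PHQ-9 "are used to monitor for the presence and severity of depressive symptoms each month". The full PHQ-9 is given to everyone every three months. At other monthly contacts it follows only a raised PHQ-2.
- **Not among the secondary measures.** Secondary outcomes and process measures does not list the PHQ, so the repeated-measures ANOVA planned for secondary outcomes does not clearly reach it.
- **A baseline exists.** Under Assessments, "PHQ assessments are completed at intake and then at monthly intervals from the fourth week of the MBCT program conducted for their cohort". The same section puts randomisation after the intake assessment.
- **Allocation.** Under Randomisation, "randomisation is stratified by: medication (currently taking antidepressants and/or mood stabilisers: yes/no); site of referral (primary care, secondary care, specialist clinic): diagnosis (bipolar disorder: yes/no);". The fourth factor is gender. Intake severity is not a factor.
- **Multilevel modelling.** The end of Economic evaluation permits it where it suits the design, without naming an outcome or a covariate.

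**The concern.** People who enter without a current episode still differ in residual symptoms, and those differences are likely to persist to some degree. A two-sample test on follow-up scores leaves that predictable variation in the error term. It also lets a chance difference between arms at intake carry over into the estimated MBCT effect for the trial at hand.

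The article itself expects DRAM to weaken group differences on standard symptom measures (Discussion). Precision on a symptom score is therefore worth having, and here it can be had from data already collected. What is at stake is the efficiency of one supporting continuous comparison.

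**Working it through.** **1. The plan's own figure.** Inputs from Power analysis: relapse 21.5% (MBCT) and 41.7% (DRAM), "using an uncorrected chi-squared statistic at 80% power and α = 0.05". Sidedness is not stated; two-sided reproduces the result. With mean proportion 0.316 and difference 0.202:

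n = [1.96·√(2·0.316·0.684) + 0.8416·√(0.417·0.583 + 0.215·0.785)]² / 0.202² = (1.2887 + 0.5401)² / 0.0408 ≈ 82 per arm.

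This agrees with the stated "sample size of 82 participants to complete the full 26 months in each of the MBCT and DRAM groups". Dividing by 0.80 gives 102.5, against a stated target of 102, a rounding difference only. Nothing below changes this calculation, which concerns relapse proportions.

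**2. What 82 per arm detects on a continuous score.** The documents give no PHQ standard deviation, target difference or correlation, so the effect is expressed in SD units:

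d = (1.96 + 0.8416)·√(2/82) = 2.8016 × 0.1562 = 0.44 SD at 80% power, unadjusted.

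This d is back-calculated from the relapse sample size. It is not a target in the plan.

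**3. Effect of adjusting for the intake score.** With correlation ρ between the intake score and one follow-up score, ANCOVA multiplies the residual variance by (1 − ρ²). Then power = Φ(2.8016/√(1 − ρ²) − 1.96), and the n per arm for 80% power is 82·(1 − ρ²), rounded up.

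| ρ (assumed) | 1 − ρ² | Power at 82 per arm | n per arm for 80% |
|---|---|---|---|
| 0 | 1.00 | 80.0% | 82 |
| 0.2 | 0.96 | 81.6% | 79 |
| 0.3 | 0.91 | 83.6% | 75 |
| 0.4 | 0.84 | 86.4% | 69 |
| 0.5 | 0.75 | 89.9% | 62 |
| 0.6 | 0.64 | 93.8% | 53 |

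The gain reaches 5 points at ρ of about 0.355. For a smaller true effect of d = 0.3, power goes from 48.4% unadjusted to 52.1% at ρ = 0.3 and 60.2% at ρ = 0.5.

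**4. Which part of the range is plausible.** Selection criteria exclude a current episode of MDD. That narrows the spread of intake scores and so tends to lower ρ. The rows for 0.2–0.3 deserve at least as much weight as those above them.

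**5. Chance imbalance at intake.** With 82 per arm the standard error of the intake difference is √(2/82) = 0.156 SD, and 1.96 standard errors is 0.306 SD. An imbalance of that size would move the unadjusted follow-up difference by 0.306·ρ: 0.09 SD at ρ = 0.3 and 0.15 SD at ρ = 0.5. Imbalance at least this large, in either direction, is expected in about 5% of trials, so these are outer values.

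**The case against.** **The PHQ is not named.** The sentence on continuous variables is generic. It fits other measures under the same heading, notably the CIDI-12 total of days depressed. The CIDI-12 is scheduled only at 12 and 24 months after the programme, so no intake value of that total is described and a two-sample test on it discards nothing. This stands. That PHQ severity falls under the sentence is an inference from the headings. It is a fair inference, because the PHQ is a severity score under the primary-outcome heading, is not listed as secondary, and has a stated intake value.

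**The PHQ may be no more than a monitor.** The primary outcome is an event, the PHQ is also the DRAM self-monitoring tool, and no PHQ contrast or time point is defined. Time to first clinical intervention sits under the same heading and is called adjunctive, so position alone does not make a measure a primary endpoint. This also stands, and it is why the point is about a supporting measure. The Discussion adds that much weight will go on time to clinical intervention, which lowers the stakes further.

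**Adjustment is not ruled out.** The multilevel clause could accommodate the intake score, the Cox covariate list is open-ended, and an article condenses the full plan. True, but the clause commits to nothing for the PHQ, and the Cox model is for time to relapse. The article does choose tests for continuous variables, and the ones it chooses are unadjusted.

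**A stronger reading to avoid.** A reader might infer that the plan expressly assigns PHQ severity to a t-test, that the trial thereby falls short of its 80% power, or that the comparison is biased. The documents support none of these. The assignment is by heading only, the stated power is for relapse proportions, and randomisation keeps the unadjusted test valid. Nor is it quite right that nothing balances intake severity: medication and referral site are allocation factors and may be related to it, though severity itself is not balanced directly.

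**Conclusion.** The point holds as a free improvement. For continuous measures under the primary-outcome heading, which by the article's structure include PHQ severity, only unadjusted two-sample tests are specified although an intake PHQ is available. The cost is efficiency on that comparison alone: roughly 2 to 4 points of power at ρ of 0.2–0.3 and about 10 points at 0.5, for d = 0.44 and 82 per arm. Every ρ here is assumed, d is derived from the relapse sample size, and the figures are for a single follow-up score under a normal approximation. The relapse analysis, its sample size and its stated power are unaffected.

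**What to change.** In Statistical analysis – Primary outcomes, add a sentence on PHQ severity. It would be analysed by ANCOVA, or by a longitudinal or multilevel model of the scheduled three-monthly PHQ-9 scores, with treatment group and the intake PHQ score as a continuous covariate. If the scores are too skewed, a rank-based ANCOVA or a proportional-odds model with the same covariate would replace it. The unadjusted t-test or Mann-Whitney test would remain as a supporting result.

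Two details belong in that sentence. Say whether the intake score is the PHQ-2 or the full PHQ-9, since the article says only that PHQ assessments are done at intake. Use the scheduled PHQ-9 scores and not those triggered by a raised PHQ-2, because the triggered scores are selected on severity.

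The cost is one sentence and one degree of freedom. An intake PHQ is already collected, so no participants, visits or staff are added. If ρ turns out to be near zero, almost nothing is lost.

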## Methods/Design

### Research design

This study is a prospective, multi-site, single (rater)-blind, RCT using a group comparison design between involving the intervention, MBCT, and a comparison condition, Depression Relapse Active Monitoring (DRAM) with follow-up over 2 years. Both interventions are provided in addition to TAU. All participants receive DRAM with half the sample randomised to additionally receive MBCT. Participants continue their usual treatment during the course of their participation in the trial. We avoid any attempts to standardise routine clinical care including medication beyond the recommendations of DRAM. The study is being conducted in compliance with the Helsinki Declaration and has been approved by the following governing ethics committees: Alfred Hospital Ethics Committee (280/07); Barwon Health Research and Ethics Advisory Committee (07/86); Monash University Standing Committee on Ethics in Research Involving Humans (CF07/1275-2007/019MCC; CF08/1031-2008000509); Peninsula Health Human Research & Ethics Committee (2007-53); Southern Health Human Research Ethics Committee (07056B); and The Melbourne Clinic Research Ethics Committee (189). Written informed consent is required for all participants.

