### The Interventions

#### MBCT

##### Description

MBCT is a manualised program delivered by an instructor in 8 weekly 2-hour group training sessions involving up to 10 clients; optional 3-monthly 'booster sessions' are also delivered. Sessions incorporate mindfulness practices including meditation and also CBT exercises [28]. Homework for participants includes formal daily meditation practices and exercises for the development of mindful awareness within everyday activity.

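### The per-protocol analyses select on session attendance in the MBCT arm only, so these supportive results can show a benefit without a treatment effect

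*Protocol article*

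**What the plan says.** Four statements in the article bear on this point.

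- Statistical analysis, Primary outcomes, sets the hierarchy: "Intention-to-treat (ITT) analysis will be the primary analytic framework". It then adds: "Per protocol (PP) analyses will also be undertaken".
- The same paragraph gives two attendance cut-offs. Citing earlier trials, "at least four sessions will be considered as the minimal treatment dose". Because the programme is sequential, "we will also examine outcomes for people who attended the recommended dose of therapy, being 7-8 sessions".
- Research design shows who can attend: "All participants receive DRAM with half the sample randomised to additionally receive MBCT". The MBCT Description says the programme is "delivered by an instructor in 8 weekly 2-hour group training sessions involving up to 10 clients".
- Power analysis supplies the anticipated 26-month relapse figures, "MBCT group 21.5%; and DRAM group 41.7" per cent.

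The article gives no adherence criterion for DRAM, although DRAM has its own monthly self-monitoring. It does not say with whom the attenders are compared.

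**The concern.** Attendance is observed after randomisation, and only the MBCT arm can meet or fail it. A set defined by attendance keeps part of one arm. With no matching DRAM criterion, the natural comparator is the DRAM arm without selection. The two groups are then no longer the ones that randomisation made alike.

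The comparison would be sound only if attendance had nothing to do with the risk of relapse. Motivation, severity and stability could each influence both, and nothing in the article suggests they do not. If those who keep coming have a better outlook anyway, their lower relapse rate will be read as an effect of MBCT. For a given prognostic contrast, the distortion grows as the attending share shrinks. The 7-8 session set cannot be larger than the four-session set, so the two results side by side could resemble a gradient with dose when there is none.

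At stake is the reading of the supportive analyses. They stand under the primary outcomes heading with no note that they are non-randomised.

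**Working it through.** **The plan's own figures.** With 70% medicated and 30% not, DRAM relapse over 2 years is 0.7 × 31% + 0.3 × 56% = 38.5%, and × 26/24 = 41.7%. MBCT is 0.7 × 15% + 0.3 × 31% = 19.8%, and × 26/24 = 21.45%, stated as 21.5%. The planned difference is 41.7 − 21.5 = 20.2 points. For two proportions "using an uncorrected chi-squared statistic at 80% power and α = 0.05", taken as two-sided, the pooled-variance formula gives 82 per arm with power 0.800. That reproduces the plan.

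**Inputs for the check.**

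- Relapse with no MBCT effect: 41.7% in both arms (Power analysis).
- f, the share of the MBCT arm meeting the attendance cut: not given; assumed.
- RR, the relapse risk of non-attenders relative to attenders when MBCT does nothing: not given; assumed.

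**Formula.** The MBCT arm as a whole still relapses at 41.7%, so f × r + (1 − f) × RR × r = 0.417, where r is the attenders' risk. Hence r = 0.417 / D with D = f + (1 − f) × RR, and the spurious benefit is 0.417 − r.

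- f = 0.7, RR = 1.5: D = 0.7 + 0.45 = 1.15, r = 36.3%, artefact 5.4 points.
- f = 0.5, RR = 1.5: D = 0.5 + 0.75 = 1.25, r = 33.4%, artefact 8.3 points, which is 8.3 / 20.2 = 41% of the planned effect.

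The same formula over a range (artefact in percentage points, D in brackets):

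| Attending share | RR 1.25 | RR 1.5 | RR 2.0 |
|---|---|---|---|
| 80% | 2.0 (1.05) | 3.8 (1.10) | 7.0 (1.20) |
| 70% | 2.9 (1.075) | 5.4 (1.15) | 9.6 (1.30) |
| 50% | 4.6 (1.125) | 8.3 (1.25) | 13.9 (1.50) |

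At RR = 1, D = 1 and the artefact is zero. At RR below 1, D is below 1, r exceeds 41.7% and the bias runs against MBCT.

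**Chance of a misleading significant result.** A second calculation states the prognostic contrast as an odds ratio and compares 82 × f attenders with all 82 DRAM completers (uncorrected chi-squared, two-sided 0.05, normal approximation). Without bias, a significant result favouring MBCT has probability 2.5%. With 60% attending and an odds ratio of 2, attenders relapse at 35.0% against 41.7%, and the probability is 11.3%. Over 40% to 90% attendance and odds ratios of 1.5 to 3, the artefact is about 1 to 15 points and the probability 3.3% to 32.5%.

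**The randomised alternative.** A complier-average effect is, in its simplest form, the intention-to-treat difference divided by f. With no effect it is (41.7 − 41.7) / 0.7 = 0, whatever the attenders' prognosis. If the planned effect is real, the four-session version gives 20.2 / 0.7 = 28.9 points and a 7-8 session version gives 20.2 / 0.5 = 40.4. The second is larger only because the divisor is smaller.

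**The case against.** The strongest reply is that the article never says attenders are compared with the whole DRAM arm. For the 7-8 session set it says only that outcomes will be examined, which would also fit a description within the MBCT arm or an adjusted analysis. A condensed article may leave the comparator and estimator to a fuller document. This stands: the comparator is an inference, and its not being named is no fault. What remains is that the criteria the article does fix are one-sided. A comparison within the MBCT arm would still contrast self-selected groups.

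The prognostic contrast and the attendance shares are also assumed. That stands too. The article offers no data on either, and the direction of bias could be the opposite one.

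A reader might infer more than the document supports:

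- *That the trial's main conclusion is at risk.* It is not; intention-to-treat is primary and does not use attendance.
- *That the attendance analyses will decide how much MBCT patients need.* The article plans no such claim. Its Discussion speaks of how much training instructors need.
- *That immortal time is built in, because people who relapse in the 8 programme weeks stop attending.* Under Procedure, the 12-month diagnostic interview takes place 12 and 24 months after the programme ends, so its look-backs largely miss those weeks. The 26 months in the power analysis leaves some ambiguity, but nothing says relapse ends attendance, and the figures above contain no such component.
- *That a false dose-response is to be expected.* It is possible under the assumptions shown, no more.

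**Conclusion.** The point holds for the supportive analyses only. As stated, the per-protocol sets filter one arm on a post-randomisation variable, and the resulting contrast is biased whenever attendance is related to prognosis. With 41.7% relapse in both arms and an assumed relative risk of 1.5, the spurious benefit is 5.4 points if 70% attend and 8.3 points if 50% attend. Those sizes rest on assumed attendance, an assumed prognostic ratio, and the inferred comparison with unselected DRAM participants. This is worth correcting because a method that keeps the randomised comparison is available with data the trial already collects.

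**What to change.** In Statistical analysis, Primary outcomes, make these changes:

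1. Make the supportive adherence analysis a complier-average causal effect at the definition of at least four sessions, with randomisation as the instrument. Include everyone randomised and adjust for the minimisation factors (medication, site of referral, diagnosis, gender). State the assumption that attending fewer than four sessions has no effect; this is in keeping with the article's own choice of four as its minimum.
2. If results for attenders are still reported, including the 7-8 session set, name the comparator, label them descriptive and non-randomised, and draw no dose-response inference from them.
3. Do not give a complier-average estimate at 7-8 sessions equal standing. It assumes that one to six sessions have no effect, which conflicts with the four-session minimum, and it would exceed the four-session estimate mechanically, as the 40.4 and 28.9 points show.

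The cost is some rewording and a little programming, with no new data or participants. The downside is wider confidence intervals than the naive per-protocol result, and an estimate that depends on one stated assumption.
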